## **15.0 Risks to Subjects\***

15.1 Laser Depilation Group Potential risks may include:

- No relief of symptoms
- Recurrence of pilonidal abscess or wound complication
- Photosensitivity or discomfort from laser treatments
- Lastly, loss of confidentiality could be a risk.

Chemical/Mechanical Depilation group:

- Loss of confidentiality could be a risk.

We believe that there is very little risk as a result of being in this study.

Laser treatment may cause some pain or discomfort during and after the laser treatment. We will be applying a topical anesthetic to the skin prior to the laser treatment and will monitor the skin closely for any significant redness or tenderness after the treatment. Trained laser operators will be in the room to make sure the laser is working safely so as to minimize any risks.

The topical anesthetic cream may cause a burning feeling on the skin, a change in color of the skin in that area, or can temporarily affect the way your blood carries oxygen, called methemoglobinemia. We will watch for any of these problems and then check on the area to see if the infection has returned or if it has gotten better as the treatments happen.

971 It is possible that the participant could feel upset when answering  
972 questions about your diagnosis or medical treatment, but it may be more  
973 likely that you find the questions or feedback process a little boring.

974 Although we will take every precaution, there is a small chance of loss of  
975 confidentiality of PHI.

976 15.2 If applicable, indicate which procedures may have risks to the  
977 subjects that are currently unforeseeable.-N/A

978 15.3 If applicable, indicate which procedures may have risks to an  
979 embryo or fetus should the subject be or become pregnant. – N/A

980 15.4 If applicable, describe risks to others who are not subjects. -N/A

## 981 **16.0 Potential Benefits to Subjects\***

982 16.1 Laser Depilation Group Potential benefits may include:

- 983 • Faster relief of symptoms (ex: resolution of pain, erythema)
- 984 • Avoiding surgery altogether
- 985 • No risk of surgical complications
- 986 • Possible decrease in folliculitis or recurrence

987 Chemical/Mechanical Depilation Group

- 988 • Possible decrease in folliculitis or recurrence due to better hair  
989 removal from multiple clinic visits
- 990 • Receipt of laser therapy upon completion of 1 year follow-up at  
991 no charge if it is shown to be effective.

992 Laser depilation treatments will be provided at no cost to the patient. All  
993 clinic visits and medications related to the study will be provided at no  
994 cost to the patient. Patients randomized to the control group will be  
995 offered laser therapy upon completion of 1 year follow-up at no charge if  
996 it is shown to be effective.

997 To assist with the costs and time spent participating in the study, a \$20  
998 research debit card will be given to the patient or their legal guardian at  
999 the end of the visit or mailed to the legal guardian's address (or patient's  
1000 address if <18 years of age) upon successful completion of the surveys.  
1001 After initial follow up, a \$20 research debit card will be mailed to the legal  
1002 guardian's address (or patient's address if <18 years of age) upon  
1003 successful completion of the surveys at 6 and 9 months. A \$50 research  
1004 debit card will be mailed the legal guardian's address (or patient's address  
1005 if <18 years of age) upon successful completion of the surveys at 12  
1006 months. Participants will not receive payment for the completion of the 18  
1007 and 24 month time points.

1008 16.2 Indicate if there is no direct benefit. Do not include benefits to  
1009 society or others. – N/A

## **17.0 Data Management\* and Confidentiality**

17.1 The means/medians and standard deviations/interquartile ranges of the prognostic variables will be evaluated in the total study sample and will be compared between groups using t-tests or Mann Whitney U tests for continuous variables and chi-squared tests for categorical variables. For the primary outcome of recurrence within one year, we will calculate this proportion and its 95% confidence interval, based on the exact binomial distribution, in both treatment groups and compare this proportion between groups using a Chi-squared test.

Other outcomes will be compared using chi square tests, if categorical, and t-tests or Mann Whitney U tests as appropriate if continuous. In analyses that include outcome data collected after patients in the control group were offered laser treatment, both intention-to-treat and per-protocol analyses (with control group patients analyzed according to the treatment they received and according to the time from the start of their laser treatment) will be performed. SAS Enterprise Guide (Cary, NC) will be used for the statistical analyses.

The sample size needed to assess the primary outcome of the proportion of patients with recurrent pilonidal disease at 1-year is based on: 1) previous published studies and institutional data on the recurrence rates of pilonidal disease and 2) the efficacy of laser hair depilation treatment to reduce pilonidal disease recurrence in previous studies and our institutional pilot study. In this RCT, the recurrence rate within 1 year is expected to be 12% in the control group and a maximum 2% in the laser group. Based on these estimated recurrence rates, under a group sequential design with one interim and one final analysis, an overall type I error rate (two- sided) of 5 % and power of 80%, the sample size required for this trial is 122 patients in each treatment group. Assuming a 10% drop out rate over the course of the 1 year follow-up, we will plan to enroll 136 patients in each group (total; n=272 patients). The total of patients increased to 302 due to reasons related to COVID described above.

Heterogeneity of treatment effects (HTE) will be formally explored for four characteristics: episodes of previous of disease, previous surgical excision performed, gender, and BMI (Figure 2: Conceptual Model). However, as the evidence regarding the effects of these factors on recurrence rates is not consistent in the literature, these HTE analyses are considered exploratory and the study will not be powered specifically for analyses of treatment effects in these subgroups

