## **4.0 Study Endpoints**

4.1 The primary outcome is the rate of recurrent pilonidal disease at 1 year defined as development of a new pilonidal abscess, folliculitis, or draining sinus after treatment, which would require antibiotic treatment, additional surgical incision and drainage, or excision within 1 year of enrollment.

Secondary outcome include: differences in disability days of the patient at 1 year, disability days of the caregiver at 1 year, HRQOL, health care satisfaction, disease-related attitudes and perceived stigma, rates of

PROTOCOL TITLE: A randomized controlled trial of laser hair depilation in adolescents with pilonidal disease

pilonidal disease-related complications, rates of pilonidal disease related procedures (incision and drainage), surgical excision, and post-operative complications, and rates of compliance with recommended treatment.

A summary of the outcomes that will be assessed are listed in the table below (Table 2).

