**Table 2: Outcomes to be assessed**

| Outcome                                          | Initial visit | 1 month | 2 month | 3 month | 4 month | 6 month | 9 month | 12 month | 18 month | 24 month |
|--------------------------------------------------|---------------|---------|---------|---------|---------|---------|---------|----------|----------|----------|
| Pilonidal disease recurrence (Primary Outcomes)  | X             | X       | X       | X       | X       | X       | X       | X        | X        | X        |
| Disability days of the patient                   | X             | X       | X       | X       | X       | X       | X       | X        | X        | X        |
| Disability days of the caregiver                 | X             | X       | X       | X       | X       | X       | X       | X        | X        | X        |
| Compliance with recommended treatment            | X             | X       | X       | X       | X       | X       | X       | X        | X        | X        |
| Pilonidal disease related complications          | X             | X       | X       | X       | X       | X       | X       | X        | X        | X        |
| Emergency Department visits                      | X             | X       | X       | X       | X       | X       | X       | X        | X        | X        |
| Readmissions                                     | X             | X       | X       | X       | X       | X       | X       | X        | X        | X        |
| Additional surgical or interventional procedures | X             | X       | X       | X       | X       | X       | X       | X        | X        | X        |
| Post-operative complications                     | X             | X       | X       | X       | X       | X       | X       | X        | X        | X        |
| Healthcare-associated costs                      | X             | X       | X       | X       | X       | X       | X       | X        | X        | X        |
| Incremental cost-effectiveness                   |               |         |         |         |         |         |         | X        |          |          |
| Satisfaction with Health Care                    |               | X       |         |         | X       |         | X       |          |          |          |
| Health Related Quality of Life                   | X             |         |         | X       |         | X       |         | X        |          |          |

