#### Baseline Assessment

Prior to the first treatment, both the patient and legal guardian will be asked to provide demographic and socioeconomic information (SES) including: age, race, ethnicity, gender, annual household income range, patient occupation (from those who work), guardian occupations and specific insurance coverage status. We will also collect a complete medical history of pilonidal disease, family history of pilonidal disease, current pilonidal disease symptoms, current hygiene regime, and history of physician office visits, Emergency Department/urgent care visits and inpatient hospitalizations for pilonidal disease.

The child and legal guardian will be asked to complete the age appropriate PedsQLTM Quality of Life Inventory and questions about healthcare associated disability, pain and pilonidal disease management. The patient will also complete the Child Attitude Toward Illness Scale (CATIS) and the parent and child will complete the disease-related stigma scales. To assist with the costs and time spent participating in the study, parking

484 costs will be paid for by the study and a \$20 research debit card will be  
485 given to the patient or their legal guardian at the end of the visit.

486 **Immediately Following/ 24hrs Post-Treatment (Intervention Group)**

487 Immediately following each laser treatment and 24 hours after, the patient  
488 will be asked to rate their pain from 1-10 utilizing the Numeric Rating  
489 Scale (NRS-11) (see Appendix for Pain Scale). Contact for the 24 hour  
490 follow-up will be completed by phone, text or email.

491 **Follow-up at 1, 2, 3, and 4 months**

492 The patient and legal guardian will complete surveys assessing healthcare  
493 associated disability, pain, pilonidal disease management, and Emergency  
494 Department/ urgent care/ physician office/hospital visits that occurred  
495 between follow-up assessments. In addition, the CATIS will be completed  
496 at the 2 month follow-up, the parent and child disease-related stigma  
497 scales will be completed at the 3 month follow-up, and the age appropriate  
498 Child and Parent PedsQLTM will be administered at the 4 month follow-  
499 up. The Healthcare Satisfaction questionnaire will be administered at the 1  
500 and 4 month follow-ups. These surveys and questionnaires will be  
501 completed at the in-person visits for patients in the laser group and by  

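### PedsQL, CATIS and stigma scores have baseline values, but Section 17.1 compares them with no baseline adjustment and no named time point, at an avoidable cost in precision

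*Combined protocol and SAP*

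**What the plan says.** Section 4.1 lists these among the secondary outcomes: "HRQOL, health care satisfaction, disease-related attitudes and perceived stigma".

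Three of the four have a baseline. Under Baseline Assessment in Section 6.4, "The child and legal guardian will be asked to complete the age appropriate PedsQLTM Quality of Life Inventory", and "The patient will also complete the Child Attitude Toward Illness Scale (CATIS) and the parent and child will complete the disease-related stigma scales". Follow-up measurements, from Table 2 and Section 6.4, are:

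- PedsQL: an early visit, then 6 and 12 months. Section 6.4 places the early visit at month 4 ("Child and Parent PedsQLTM will be administered at the 4 month"). The Table 2 row "Health Related Quality of Life" is marked at month 3.
- CATIS: 2, 6 and 12 months.
- Stigma: 3 and 9 months.
- Healthcare satisfaction: 1, 4 and 9 months, with no baseline.

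For the analysis, Section 17.1 says: "Other outcomes will be compared using chi square tests, if categorical, and t-tests or Mann Whitney U tests as appropriate if continuous". It does not say whether the tested variable is a follow-up score, a change from baseline or a summary over visits, and it names no visit. Its comparison of prognostic variables between groups describes baseline balance and adjusts nothing. The paragraph on heterogeneity of treatment effects names no model and no baseline scale score. No ANCOVA, regression or mixed model appears anywhere in the document.

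**The concern.** A patient's score before treatment usually predicts the later score. A two-sample comparison of follow-up scores leaves that predictable part in the error term. Baseline adjustment removes it, and the baseline questionnaires are already being collected.

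The only sample-size calculation concerns recurrence, so the precision of the patient-reported scales depends on how they are analysed. With no analysis variable and no visit fixed, each scale also allows several possible results in a trial where participants and staff know the assignment (Section 17.2). What is at stake is the width of the intervals for three secondary scales, and whether one estimate per scale is settled in advance.

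**Working it through.** **Inputs from the plan (Sections 12.1 and 17.1).** Two-sided 5% type I error, 80% power, expected recurrence of 12% and 2%, 122 evaluable per arm, 10% drop-out, 136 per arm (272 in total), later 302. Allocation is balanced (Section 17.2).

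**Inputs not in the plan (assumed).** The correlation r between baseline and follow-up score, taken as 0.3 to 0.7; a difference of 0.3 SD; scores standardised to SD = 1.

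**The plan's own figure.** For 12% against 2%, the pooled normal formula gives (1.96·√(2·0.07·0.93) + 0.842·√(0.12·0.88 + 0.02·0.98))² / 0.10² ≈ 101.0, so 102 per arm. The continuity correction, (101.0/4)·(1 + √(1 + 4/(101.0·0.10)))² ≈ 120.2, gives 121, against 122 stated. An O'Brien-Fleming-type early look spends less than 0.0001 of alpha and barely changes this. Then 122/0.90 = 135.6, so 136, and 272 + 30 = 302. The figure of 122 reproduces to within one patient and is used below as the evaluable number per arm.

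**Variance at one visit, relative to an unadjusted comparison of follow-up scores (= 1).**

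- Baseline-adjusted (ANCOVA): 1 − r²
- Change score: 2(1 − r)

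**Equivalent sample size:** 122/(1 − r²).

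**Power:** Φ(0.3·√(122/2)/√(1 − r²) − 1.96). Unadjusted: 0.3·7.81 = 2.343, and Φ(0.383) = 65%.

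**Difference detectable at 80% power:** 2.80·√(2/122)·√(1 − r²). Unadjusted: 0.359 SD.

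| r | ANCOVA variance | Variance cut | Change-score variance | 122 per arm is worth | Power at 0.3 SD | Detectable difference |
|---|---|---|---|---|---|---|
| none used | 1.00 | – | – | 122 | 65% | 0.359 SD |
| 0.3 | 0.91 | 9% | 1.40 | 134 | 69% | 0.342 SD |
| 0.5 | 0.75 | 25% | 1.00 | 163 | 77% | 0.311 SD |
| 0.7 | 0.51 | 49% | 0.60 | 239 | 91% | 0.256 SD |

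If Section 17.1 means change scores, ANCOVA is still more precise at each r. At r = 0.3 a change-score test is worse than ignoring baseline (1.40 against 1.00).

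**Simulation check.** With 2,000 runs, 122 per arm and a true difference of 0.359 SD, power was about 79–80% for the t-test and 77–78% for Mann-Whitney. For ANCOVA it was 83%, 90% and 98% at r = 0.3, 0.5 and 0.7.

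**The case against.** The strongest reply is that nothing here is invalid. Under randomisation the unadjusted test keeps its error rate, and its interval already allows for chance imbalance at baseline. A reader might infer from the unstratified design that imbalance biases these results. The documents do not support that: the characteristics considered for stratification in Section 17.2 were judged by their association with recurrence, and nothing shows that stratifying on them would balance these scales. This part of the objection stands; the point is about efficiency and pre-specification.

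The size depends on inputs the documents do not give. A year between measurements with treatment in between, and age-appropriate forms for patients aged 11 to 21, leave no ground for excluding a low r. At r = 0.3 the gain is modest. This also stands, which is why the whole range is shown.

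Three further inferences are tempting but unsupported:

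- That the plan definitely discards the baseline, or tests every visit separately. Section 17.1 is silent on both.
- That every patient-reported secondary outcome loses precision. Healthcare satisfaction has no baseline, so adjustment cannot help it.
- That modelling all visits together would sharpen the 12-month estimate much further. With complete data, earlier visits add essentially nothing to that contrast. Their main use is to retain patients with partial follow-up, which is relevant given the expected 10% drop-out and the COVID-19 disruption.

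The month 3 and month 4 discrepancy for PedsQL is a separate inconsistency. It does not alter a 12-month comparison, and it does not show that patients are assessed at different visits.

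**Conclusion.** The point holds for PedsQL, CATIS and stigma. Section 17.1 gives a valid but inefficient comparison, with no baseline adjustment and no analysis visit, although each scale has a baseline and two or three follow-ups. The variance cut is 9% to 49% at one visit relative to a follow-up-score test, if r lies between 0.3 and 0.7. To speak of a large loss without qualification would assume the upper part of that range. The power figures also rest on the assumed 0.3 SD difference and 122 evaluable patients per arm. The recurrence endpoint, its sample size and its error rate are untouched. The change is worth making because the better method uses data already collected.

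**What to change.** In Section 17.1, replace the general sentence for these three scales with a stated model. Use either ANCOVA at the named visit with baseline score and arm, or a mixed model for repeated measures with baseline score, visit, arm and arm-by-visit. Report the adjusted difference with its 95% CI at 12 months for PedsQL and CATIS and at 9 months for stigma, with child and parent reports analysed separately where both exist. Healthcare satisfaction can keep a two-sample comparison, with its visit named.

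Separately, reconcile Table 2 with Section 6.4 on the treatment-phase PedsQL visit, so that a repeated-measures model has one agreed schedule.

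The cost is a few sentences of analysis plan and standard code in SAS, which the plan already uses. It needs no new data and no extra patients.

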For patients with recurrent disease, there are both medical and surgical methods to treat and/or palliate pilonidal disease. Each of these methods incurs a different risk-benefit profile and has been associated with significant morbidity. Overall, surgical methods appear to be more durable with long term success rates ranging from 84 to 89%. However, surgical excision and reconstruction of this area can be associated with significant morbidity and cost. Recurrence rates of pilonidal disease after resection have been reported to be 11%. Furthermore, wound issues after resection with primary closure have been reported to be as high as 30%. Medical therapy is largely dependent upon continued lifelong hair removal either from shaving or chemical depilation, meticulous hygiene to the area, and recurrent courses of antibiotics with intermittent need for both office-based, and operating room incision and drainage procedures. This approach to pilonidal disease incurs a chronicity that can lead to longer term disability and reduced quality of life. In fact, the presence of pilonidal disease and its complications is an accepted indication for Disability Insurance qualification. It has been noted by several authors that an optimal treatment for pilonidal disease has yet to be identified.

A historical chart review (IRB 16-00648) of patients with pilonidal disease treated at Nationwide Children's Hospital (NCH) demonstrated an overall recurrence rate of 36% with recurrence rates of 32% after initial treatment with antibiotics, 36% after an incision and drainage procedure, and 35% after surgical excision. The 1 year recurrence rate is 20%; therefore, the majority of patients that experience a recurrence will do so in the first year. These high rates necessitate identifying treatments that can effectively decrease the recurrence of pilonidal disease.

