533 adverse events for this study. If these patients choose to receive the  
534 elective laser treatments, they will be brought back into the clinic and re-  
535 consented by the study staff prior to their first treatment. They will have  
536 the option to commit to one or two additional years in the study and will  
537 be followed in the same manner as the patients initially randomized to the  
538 laser intervention group. Data will be collected from the patients per the  
539 same follow-up surveys at 1, 2, 3, and 4 months and post-treatment  
540 follow-up surveys at 6, 9, 12, 18, and 24 months after their initial visit. A  
541 \$20 research debit card will be mailed to the legal guardian's address (or  
542 patient's address if  $\geq 18$  years of age) upon successful completion of the  
543 surveys at 6 and 9 months. A \$50 research debit card will be mailed the  
544 legal guardian's address (or patient's address if  $\geq 18$  years of age) upon  
545 successful completion of the surveys at 12 months. Since laser therapy has  
546 previously been shown to be safe and tolerable, patients and caregivers in  
547 the control group will be informed of the safety monitoring data and the  
548 recurrence rates from the interim analysis when available (Analysis  
549 section above) and allowed to decide if they would like to receive laser  
550 therapy.

551 Subjects who will turn 18 before their 12, 18, or 24 month follow-up will  
552 be asked to sign the informed consent used for the study and to update  
553 their contact information. After speaking with the subject and explaining  
554 the study, an informed consent and contact information sheet will be  
555 mailed to the subjects to sign so that we may continue to collect data up to  
556 24 months after their initial study treatment.

557 **6 months post 1st treatment ( $\pm 30$  days)**

558 A member of the research team from NCH will contact the family over the  
559 phone or email and ask questions about any problems the child has had  
560 with their pilonidal disease since their 30-day follow-up. Specifically, we  
561 will ask about subsequent ED/Urgent Care visits or physician visits,  
562 readmissions and operations, additional imaging, and missed days from  
563 normal activities by the patient and legal guardian that were related to  
564 their pilonidal disease. We will also ask about the out-of-pocket

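### After month 12, the analysis labelled per-protocol is an as-treated comparison with a restarted clock for self-selected controls, and neither it nor ITT is named as the lead analysis

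*Combined protocol and SAP*

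**What the plan says.** The rule is in section 17.1. Its scope is limited: "In analyses that include outcome data collected after patients in the control group were offered laser treatment". For those analyses the plan performs "both intention-to-treat and per-protocol analyses", the latter with "control group patients analyzed according to the treatment they received and according to the time from the start of their laser treatment". It does not say which of the two leads.

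The tests named in 17.1 are chi-squared, t and Mann-Whitney tests. For the primary outcome the plan will "compare this proportion between groups using a Chi-squared test"; "Other outcomes will be compared using chi square tests" when categorical.

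Section 6.4 says that controls who elect laser at 12 months are re-consented, may commit to one or two more years, and will "be followed in the same manner as the patients initially randomized to the" laser group. They choose after being told the safety data and, when available, the interim recurrence rates. The Study Summary keeps controls who decline on their original 18- and 24-month schedule. Table 2 collects recurrence, disability days, complications and costs at 18 and 24 months.

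The primary endpoint precedes the offer: "The primary outcome is the rate of recurrent pilonidal disease at 1 year" (section 4.1).

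**The concern.** A per-protocol analysis normally keeps patients in their assigned arm and restricts to those who followed the protocol. The rule in 17.1 instead reclassifies patients by the treatment they took, and sets their time zero at their own laser start. Three things then separate the groups besides laser:

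- **Selection.** Controls choose laser themselves, in an open trial, knowing interim results. The controls left at 18 and 24 months are those who said no.
- **Time.** A crossover patient's month 0 is at least 12 months after entry. Section 3.1 says of the historical series: "The 1 year recurrence rate is 20%; therefore, the majority of patients that experience a recurrence will do so in the first year". If risk also falls with time since trial entry, the restarted year is a lower-risk year.
- **Dependence.** If a patient's control year is kept and the laser period is added, one person contributes to both groups, and the named tests treat the two as independent.

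The rule also leaves open whether the control year is kept, and whether crossover patients are pooled with the randomised laser arm or shown separately. With two analyses standing level and no lead named, a disagreement between them could be settled after the results are seen.

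**Working it through.** **1. The plan's own figure.** Section 17.1 gives 12% versus 2%, two-sided 5%, 80% power, 122 per arm, and 136 after 10% dropout. With mean rate 0.07 and d = 0.10:

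- n = [1.960·√(2·0.07·0.93) + 0.842·√(0.12·0.88 + 0.02·0.98)]² / 0.10² = 101.0, rounded up to 102.
- With continuity correction: (101.0/4)·[1 + √(1 + 4/(101.0·0.10))]² = 120.2, rounded up to 121, against the stated 122.
- 122/0.90 = 135.6, rounded up to 136.

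An O'Brien-Fleming-type look at about a quarter of the information adds less than 0.1%. The sample size stands and concerns only the 1-year comparison. The documents give no figure for the analysis after month 12.

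**2. Later risk.** Section 3.1 gives 20% at 1 year and 36% overall, with no stated length of follow-up. Among those free of recurrence at 1 year, later risk is 1 − 0.64/0.80 = 20%. Spread over an assumed four years this is about 5% a year, a quarter of the first-year risk. If all of it fell in year 2, it would be 20% and there would be no decline. I therefore vary the ratio of year-2 to year-1 risk.

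**3. No laser effect, both periods kept, crossover patients pooled with the laser arm.** With first-year risk p1, crossover risk p2 and crossover share f, pooled laser risk = (p1 + f·p2)/(1 + f). Control risk is p1. The last column is the chance of a significant result favouring laser (122 per arm, chi-squared without continuity correction, observations treated as independent; nominal about 2.5%).

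| p1 | p2 | f | Laser | Control | False benefit |
|---|---|---|---|---|---|
| 12% | 3% | 0.5 | 9.0% | 12.0% | 14% |
| 12% | 3% | 0.9 | 7.7% | 12.0% | 27% |
| 12% | 6% | 0.5 | 10.0% | 12.0% | 8.5% |
| 12% | 12% | 0.5 | 12.0% | 12.0% | about 2.5% |
| 20% | 5% | 0.5 | 15.0% | 20.0% | 21% |
| 20% | 5% | 0.9 | 12.9% | 20.0% | 42% |
| 20% | 20% | 0.5 | 20.0% | 20.0% | about 2.5% |

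First row: (12 + 0.5·3)/1.5 = 9.0.

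**4. The other reading: crossover patients leave the control group.** Take a 12% first-year risk, constant over time, no laser effect, and patients who differ in underlying risk (gamma frailty, shape 1, assumed). The recurrence rate among the controls who stay follows directly:

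- Patients with a recurrence cross over less (20% versus 60%): (0.8·0.12)/(0.8·0.12 + 0.4·0.88) = 21.4%, against 11.7% in pooled laser. False benefit 45%.
- Patients with a recurrence cross over more (90% versus 40%): (0.1·0.12)/(0.1·0.12 + 0.6·0.88) = 2.2%, against 12.3% in pooled laser. False harm 77%.

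With the same two selection patterns but both periods kept, pooled laser is 11.7% or 12.3% against 12.0%, so selection alone then does little. If patients with a recurrence cross over more and year-2 hazard is a quarter of year-1 hazard, laser is 9.3% against 11.9% with both periods kept, and 9.3% against 2.2% with crossover patients removed. The sign depends on a choice that 17.1 does not make.

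**The case against.** The strongest reply is that little rests on this rule. The primary outcome is measured before the offer, section 4.1 names no 18- or 24-month endpoint, and 17.1 already requires ITT beside the disputed analysis. All of that stands and limits the weight of the point. It does not settle which analysis leads after month 12 or make the second one interpretable.

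Four stronger readings are tempting, and the documents do not support them:

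- **That crossover patients are counted twice.** 17.1 does not say that their control year is kept, or that they are pooled with the randomised laser arm. The supportable point is that the rule is unspecified.
- **That the bias mostly favours laser.** The historical 20% and 36% come from a chart review of recurrence after initial treatment. The trial enrols patients with a previous diagnosis and no limit on time since the episode, so entry is not disease onset. The 0.64/0.80 step also applies only to patients still free of recurrence. Step 4 shows bias in both directions.
- **That the bias is half the planned effect.** That sets about 5 points on a 20% base against a 10-point effect planned from 12% versus 2%. On the 12% base it is about 3 points.
- **That the main result is compromised.** It is not.

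A further reply is that the no-effect scenario may not arise, since section 16.1 and the 12-month paragraph of 6.4 offer laser only if it is shown effective. This stands in part. However, the Study Summary states no such condition, section 6.4 elsewhere makes the offer contingent on interim adverse-event analyses, and controls reach month 12 at different dates, while the final analysis waits for all patients to complete a year. If laser does work, the same mechanisms would distort the estimated size of its effect.

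**Conclusion.** The point holds, as a moderate defect in the analyses after month 12. The analysis labelled per-protocol is as-treated and non-randomised, restarts the clock for self-selected patients, leaves pre- and post-laser time unassigned, and stands level with ITT.

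Its size cannot be fixed from the documents. With no laser effect, half of controls crossing over, later risk a quarter of first-year risk and both periods kept, the spurious difference is 3 points on the plan's 12% rate or 5 points on the historical 20%, with a 14% or 21% chance of a false significant benefit. It is zero under constant risk with both periods kept. It goes clearly against laser if patients with a recurrence elect laser more often and are removed from the control group. The crossover share, the later risk and the selection pattern are all assumptions. The figures describe 12-month risk on the restarted clock; no 18- or 24-month size was computed.

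**What to change.** In 17.1:

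1. Drop the label per-protocol.
2. Name ITT by randomised arm, timed from randomisation, as the lead analysis for all data after month 12.
3. Replace the bracketed rule with a supportive analysis timed from randomisation, in which control follow-up is censored at first elective laser, or laser enters as a time-dependent exposure. Control time before laser then stays with control. Label it non-randomised and open to informative censoring.
4. Report controls who elect laser as a separate single-arm descriptive cohort from laser start, not pooled with the randomised laser arm.

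Separately, reconcile the passages on when controls are offered laser (Study Summary; section 6.4, post-treatment follow-up and 12-month paragraphs; section 16.1), because they determine who crosses over.

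The cost is SAP wording and minor programming. The downsides are a smaller laser sample in the supportive analysis and residual selection bias from the censoring.
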